### Study endpoints

#### Primary endpoints

As the pro-inflammatory cytokine IL-6 is consistently upregulated following intra-abdominal sepsis or injury and has been reported to correlate with outcomes (Table 
2), the primary endpoint is the difference in the plasma concentration of IL-6 at 24 and 48 h after dressing application between patients randomized to TAC with the ABThera™ *versus* Barker’s vacuum pack after damage control laparotomy.

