#### Secondary endpoints and exploration of clinical efficacy and safety

Secondary endpoints of interest include trial feasibility (number of patients enrolled/number of eligible candidates) and the differential effects of the allocated TAC dressings on several physiological and organ dysfunction outcomes, including: (1) the plasma concentration of TNF-α and IL-1, -8, -10, and −12 at 24 and 48 h; (2) the collective peritoneal and systemic mediator profiles (see below); (3) the activation potential of peritoneal fluid
[70,71]; (4) peritoneal fluid drainage volume; (5) postoperative daily fluid balance; (6) SOFA scores and individual organ system components of these scores; (7) the PaO_2_/FIO_2_ ratio; (8) vasopressor requirements and arterial lactate levels; (9) need for renal replacement therapy; (10) RIFLE criteria; (11) APACHE-II scores; and (12) 24 h enteral tolerance (if no gastrointestinal anastomosis was performed).

Secondary clinical efficacy and safety endpoints of interest include: (1) in-hospital death; (2) fascial closure rate and days with fascial closure for the month after admission to hospital; (3) ventilator-free days for the month after admission to hospital; (4) ICU-free days from the month after admission to hospital; (5) hospital-free days from the month after admission to hospital; and (6) risk of renal replacement therapy and days free of renal replacement therapy from the month after admission to hospital. Further, as some have suggested that negative pressure peritoneal therapy may be associated with an increased risk of abdominal fistula formation or development of intra-abdominal hypertension/recurrent abdominal compartment syndrome
[72-74], additional safety outcomes include: (1) intestinal and enteroatmospheric fistula formation; (2) daily IAP; (3) daily WSACS intra-abdominal hypertension grading classification; and (4) risk of abdominal compartment syndrome development.

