### Statistical analyses

All continuous variables will be summarized using histograms and measures of central tendency to determine their underlying distribution before statistical descriptions or analyses are conducted. Means (with standard deviations) and medians (with interquartile ranges) will be used to summarize normal and skewed data, respectively. Non-correlated means and medians will be compared using t-tests and Wilcoxon rank sum tests while dependent means and medians will be compared using paired t-tests and Wilcoxon signed rank tests. Differences in proportions will be compared using Fisher’s exact test and risk ratios with associated 95% confidence intervals.

For the analysis of the primary endpoint, we will use a mixed-effects repeated measures linear model to compare the effects of the ABThera™ and Barker’s vacuum pack on changes in plasma IL-6 concentration at 24 and 48 h after TAC dressing application
[75,76]. For longitudinal studies, mixed-effects models have previously been shown to be superior to conventional last-observation-carried-forward approaches for handling missed observations during follow-up
[77,78]. This approach will also be used to compare the plasma concentrations of TNF-α and IL-1, -8, -10, and −12 between groups at 24 and 48 h in the analysis of secondary endpoints.

Multidimensional analysis will be used to assess whether the allocated TAC dressing has an effect on the collective peritoneal and plasma mediator profiles of the study patients. Principal components analysis will be used to reduce the mediator concentration variables into a smaller set of components that account for most of the variability in the data. Component scores will subsequently be calculated along the reduced number dimensions, after which we will attempt to distinguish between patients treated with the ABThera™ and Barker’s vacuum pack using discriminant or latent class analysis. A similar approach will be performed in order to relate inflammatory mediator concentrations to outcomes.

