Results will be stratified according to the primary indication for damage control laparotomy (intra-abdominal sepsis or abdominal trauma). While clinical efficacy and safety data will be analyzed according to intention-to-treat methods, mediator data will be examined using per-protocol techniques, with per-protocol treatment being defined as the allocated TAC dressing having been in place for at least 24 h. As the number of conducted statistical tests will be large, we will use the false discovery rate (FDR) procedure developed by Benjamini and Hochberg to restrict the proportion of incorrectly rejected null hypotheses to 0.05
[79-81]. All tests will be two-sided, and only those with an FDR-corrected *P* value (that is q-value) <0.05 will be considered statistically significant
[79]. Stata version 12.0 (Stata Corp., College Station, TX, USA) will be used for all analyses.

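### The false discovery rate rule covers every test, so the criterion for the primary IL-6 endpoint depends on the other tests, and safety differences must clear the same hurdle

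*Protocol article*

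**What the plan says.** Under Primary endpoints, the protocol article names one primary endpoint, "the difference in the plasma concentration of IL-6 at 24 and 48 h after dressing application". Under Statistical analyses it assigns that endpoint a single model: "we will use a mixed-effects repeated measures linear model to compare the effects" of the two dressings at 24 and 48 h.

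The section on secondary endpoints adds five further cytokines ("the plasma concentration of TNF-α and IL-1, -8, -10, and −12 at 24 and 48 h"), a list of physiological and organ-dysfunction measures, and six clinical efficacy and safety endpoints. It then adds outcomes chosen because harm is suspected: "additional safety outcomes include: (1) intestinal and enteroatmospheric fistula formation", abdominal pressure, its grading, and abdominal compartment syndrome. Results are also to be stratified by indication (sepsis or trauma).

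The multiplicity rule closes Statistical analyses: "As the number of conducted statistical tests will be large, we will use the false discovery rate (FDR) procedure". The Benjamini-Hochberg procedure is used "to restrict the proportion of incorrectly rejected null hypotheses to 0.05". The scope follows: "All tests will be two-sided, and only those with an FDR-corrected" value below 0.05 count as significant. The section does not divide the tests into families, state their number, set the primary endpoint apart or exempt safety.

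**The concern.** A prespecified primary endpoint should succeed or fail on its own data. In a Benjamini-Hochberg pool of m tests, a P value is compared with 0.05k/m, where k is the number of rejections. If IL-6 is in the pool, its threshold moves with results for SOFA, fluid balance or fistula, and with an m that is not stated. The criterion for the primary question is then unknown in advance, and its type I error depends on unrelated endpoints.

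For safety, multiplicity correction mainly guards against false claims of benefit. Applied to fistula or compartment syndrome, it raises the bar for flagging harm in a trial whose Discussion makes intervention safety a pilot aim.

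**Working it through.** **Inputs.** From the article: 46 patients (Sample size), equal groups (Patient randomization), so 23 per arm; error level 0.05, two-sided. Assumed, because the article gives no effect, SD or power: an IL-6 effect of 0.845 SD, chosen because it gives 80% power for one t-test at 0.05; correlation 0.6 between the two IL-6 time points; all other tests independent. The 46 is a declared convenience sample, so there is no planned power figure to reproduce. Mediator data are analysed per protocol, so 23 per arm is an upper limit.

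**Number of tests (a count from the listed endpoints, not a figure in the article).**
- One test per listed endpoint: 1 (IL-6) + 5 (other cytokines) + 11 (other physiological items) + 6 (clinical) + 4 (safety) = 27, or 28 if vasopressors and lactate, listed as one item, count as two.
- Split by time point and component: 2 + 10 + 12 + 6 (SOFA components) + 12 (clinical and safety, compound items split) = 42.
- Overall plus two strata: 3 × 42 = 126.

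**Threshold for a lone signal, 0.05/m.** 0.05/28 = 0.0018; 0.05/42 = 0.0012; 0.05/126 = 0.0004.

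**One IL-6 test as a lone signal.** The noncentrality is 0.845 × √(23/2) = 2.87 on 44 degrees of freedom. Power is 80% at 0.05, 29% at 0.05/42 and 19% at 0.05/126.

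**Either IL-6 time point, full Benjamini-Hochberg procedure (simulation, normal approximation).**

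| Setting | Power, at least one time point |
|---|---|
| IL-6 as its own family (m = 2) | about 86% |
| One pool, m = 42, nothing else true | about 50% |
| One pool, m = 126, nothing else true | about 38% |
| One pool, a quarter of the others true at 1.0 SD | about 76 to 77% for both m |

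**Type I error for IL-6 when it is truly null (either time point).** About 5% as its own family. In one pool of 40 or 120 tests it is about 0.1 to 0.3% if everything else is null, and about 7% if three quarters of the tests truly differ by 1.2 SD.

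**Safety.** Take 8/23 v 1/23 as an illustration.
- Fisher's exact P = 0.022. It is rejected only if 0.05k/m ≥ 0.022. With the unrounded P of 0.02196, k ≥ 0.02196 × 42/0.05 = 18.4, so 19 rejections of 42; or k ≥ 0.02196 × 126/0.05 = 55.3, so 56 of 126.
- Risk ratio (8/23)/(1/23) = 8.0. The SE of its log is √(1/8 − 1/23 + 1/1 − 1/23) = 1.02, giving a 95% CI of about 1.1 to 59.
- With no events in one arm, 5 v 0 reaches P = 0.049 unadjusted. A lone signal in the pool needs 10 v 0 (P = 0.00056, m = 42) or 11 v 0 (P = 0.0002, m = 126).

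**The case against.** The strongest reply is that this is a small pilot with a declared and recognised error-control method. The Overview says that the trial may not suffice to establish superiority, and the Discussion admits that it may be underpowered. The article also does not say outright that one pool is used; families could be set in an analysis plan that is not shown. This lowers the severity but does not remove the point. The published sentence covers all tests without exception, and a plan that tested IL-6 alone at 0.05 would depart from it.

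Four stronger readings might be inferred, and the documents do not support them.

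- **That the primary competes with a known number of exploratory tests.** No number is stated, and most of the tests counted above are named secondary or safety endpoints.
- **That the trial gives up most of its power.** This is the worst case only. The procedure is adaptive, so the loss shrinks as other tests reject. The Background cites animal data in which TNF-α, IL-1β, IL-6 and IL-12 fell together, so an isolated IL-6 effect is not what the rationale expects.
- **That harm signals are suppressed.** Statistical analyses already plans risk ratios with 95% confidence intervals for proportions and states no adjustment of those intervals. What is lost is the significance label. Power for harm is low even without correction: 22% for 20% v 5% at 23 per arm.
- **That naming two time points leaves the primary undefined.** One repeated-measures model is planned and allows a single joint test. Which contrast is used is detail that an analysis plan may settle.

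**Conclusion.** The point holds as a should-fix. The stated rule gives the primary endpoint no family of its own and safety no exemption. On the single-pool reading, the IL-6 criterion therefore depends on the number and results of the other tests. The cost is real but variable: from about 86% power to between 38% and 50% if nothing else differs, or to about 76 to 77% if a quarter of the other tests do. Type I error for IL-6 can also fall far below 5% or rise slightly above it. These figures rest on the assumed effect, correlation, independence and test count. For safety, a difference like 8/23 v 1/23 would probably not be called significant, since about 44% of all tests (19/42 or 56/126) would have to reject, but its estimate and interval would still be seen. The trial's pilot purpose and its admission of low power keep this below a must-fix.

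**What to change.** State three things in the analysis section before any analysis by arm:

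1. IL-6 is tested as its own family at two-sided 0.05 from the planned mixed model, outside the false discovery rate rule. Use one prespecified test, either joint or averaged over 24 and 48 h, and show both time-specific estimates with 95% confidence intervals.
2. The Benjamini-Hochberg procedure applies only to the secondary and exploratory endpoints.
3. Safety endpoints, including continuous ones such as abdominal pressure, are read from unadjusted estimates with 95% confidence intervals and are not subject to the rule.

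This takes a few sentences and needs no further patients or data. The downside is that safety results carry no multiplicity control and must be labelled so, since some nominal differences will arise by chance.

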## Discussion

This will be the first study to compare the systemic inflammatory response among critically ill or injured adults fitted with a TAC that may provide active negative pressure peritoneal therapy with a commonly used TAC technique that provides potentially less efficient peritoneal negative pressure, the Barker’s vacuum pack
[10]. This study aims to afford a robust prospective description of the peritoneal and systemic inflammatory response after damage control laparotomy for intra-abdominal sepsis or injury. A secondary aim is to gather necessary pilot information related to trial feasibility, intervention safety, and design deficiencies needed to inform construction of a multicenter RCT comparing clinical outcomes among patients fitted with the ABThera™ *versus* Barker’s vacuum pack.

In this trial, study patients in both treatment arms will undergo planned re-operation with attempts at abdominal fascial closure approximately 24 to 72 h after damage control laparotomy. Although one RCT (the RELAP trial) reported that planned re-laparatomy after an initial emergency laparotomy for secondary peritonitis resulted in increased healthcare utilization and costs as compared to re-laparotomy on demand
[82,83], these findings likely cannot be generalized to our study’s source population. In the RELAP trial, the investigators excluded patients that were managed with temporary operative techniques such as intra-abdominal gauze packing and stapled intestinal resections without reanastomosis
[82]. Moreover, 89% of the patients allocated to planned re-laparotomy received intraoperative primary abdominal fascial closure
[82]. Thus, very few, if any, of the patients in the planned re-laparotomy group likely received damage control laparotomy.

Several difficulties were encountered in designing the Intra-peritoneal Vacuum trial. The trial is demanding for study investigators as damage control laparotomy must be performed emergently and is often done at night in our center when research coordinators and laboratory members are unavailable. For these reasons, the randomization interface and enrollment process were simplified in order to prevent delays in application of the TAC device, which could alter patient outcomes. Further, as no objective, evidence-based consensus indications for damage control laparotomy or open abdominal management have yet been described, we were forced to utilize a pragmatic study design, which attempts to mimic actual surgical practice. However, in order to increase understanding, we planned *a priori* to conduct a nested prospective cohort study that will explore indications used for open abdominal management among attending trauma and general surgeons at our center.

As compared to previous translational human studies of physical therapies to reduce peritoneal and systemic inflammation among critically ill adults, this trial will utilize novel laboratory analyses and rigorous statistical techniques. In order to avoid bias with regards to which mediators are measured, we will use the validated Luminex® multiplexing technology to assay a host of pro-inflammatory mediators simultaneously in a cost- and time-efficient manner, maximizing use of the obtained patient samples
[69]. Further, although many authors have conducted comparisons of cytokine concentrations with study endpoints, they frequently ignore the correlation between mediators measured within individual patients over time. Thus, when examining the relationship between cytokines and TAC method, we will use validated statistical techniques that estimate and incorporate this correlation, and which appropriately handle missed observations during follow-up. Finally, in order to collectively analyze the difference in multiple measured mediators between TAC treatment groups, we will also use multidimensional analyses, including principal components analysis.

This trial has limitations. Although we will be combining the inflammatory mediator concentrations and outcome data for patients with both intra-abdominal sepsis and injury, which may be different, we will stratify our analyses to examine if differences exist between patient diagnoses. Moreover, as the primary objective of this trial is to explore the influence of active abdominal therapy on the systemic inflammatory response among critically ill or injured adults, we will principally use a per-protocol method of analysis. As this method of analysis may not be appropriate or as clinically useful for the exploration of safety and efficacy, we will also utilize an intention-to-treat method of analysis when comparing these endpoints. Importantly, however, as we were unable to estimate the required sample size, we may be underpowered to detect differences in the plasma pro-inflammatory mediator concentrations (or clinical and safety endpoints) among patients randomized to TAC with the ABThera™ *versus* Barker’s vacuum pack.

In conclusion, the Intra-peritoneal Vacuum Trial will be a single-center RCT. Results from this study will lead to an improved understanding of the effect of active negative pressure peritoneal therapy on the systemic inflammatory response to intra-abdominal sepsis or injury after damage control laparotomy. The study will also gather pilot information needed to inform creation of a future multicenter RCT comparing clinical outcomes among those undergoing TAC with the ABThera™ *versus* the Barker’s vacuum pack after damage control laparotomy.

## Trial status

The first patient was enrolled into the Intra-peritoneal Vacuum Trial on 29 September 2011, and we are still actively recruiting patients. At the time of writing this manuscript, 37 patients had been enrolled into the trial, the majority of which have already given delayed informed consent for use of their data. Final results of the study are expected to be prepared for publication near the conclusion of 2013.

## Abbreviations

APACHE-II: Acute physiology and chronic health evaluation-II; ELISA: Enzyme-linked ImmunoSorbent assay; ESKD: End stage kidney disease; FIO2: Fraction of inspired oxygen; FMC: Foothills medical center; IAP: Intra-abdominal pressure; KCI: Kinetic Concepts Inc; ICU: Intensive care unit; ISS: Injury severity score; PaO2: Partial pressure of arterial oxygen; RCT: Randomized controlled trial; RIFLE: Risk injury, failure, loss, and end-stage-kidney-disease; SOFA: Sequential organ failure assessment; TAC: Temporary abdominal closure; WSACS: World Society of the Abdominal Compartment Syndrome
